## Abstract

**Background:**

Millions of people in Germany suffer from chronic pain, in which course and intensity are multifactorial. Besides physical injuries, certain psychosocial risk factors are involved in the disease process. The national health care guidelines for the diagnosis and treatment of non-specific low back pain recommend the screening of psychosocial risk factors as early as possible, to be able to adapt the therapy to patient needs (e.g., unimodal or multimodal). However, such a procedure has been difficult to implement in practice and has not yet been integrated into the rehabilitation care structures across the country.

**Methods:**

The aim of this study is to implement an individualized therapy and aftercare program within the rehabilitation offer of the German Pension Insurance in the area of orthopedics and to examine its success and sustainability in comparison to the previous standard aftercare program.

The study is a multicenter randomized controlled trial including 1204 patients from six orthopedic rehabilitation clinics. A 2:1 allocation ratio to intervention (individualized and home-based rehabilitation aftercare) versus the control group (regular outpatient rehabilitation aftercare) is set. Upon admission to the rehabilitation clinic, participants in the intervention group will be screened according to their psychosocial risk profile. They could then receive either unimodal or multimodal, together with an individualized training program. The program is instructed in the clinic (approximately 3 weeks) and will continue independently at home afterwards for 3 months. The success of the program is examined by means of a total of four surveys. The co-primary outcomes are the Characteristic Pain Intensity and Disability Score assessed by the German version of the Chronic Pain Grade questionnaire (CPG).

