### Trial design {8}

Multicenter intervention trial: A randomized controlled prospective longitudinal intervention study (RCT) will be conducted at several hospitals in the regions of Berlin-Brandenburg and Central Germany. The study includes a total of four measurement points: at rehabilitation clinic admission (t0: baseline), at the end of the rehabilitation stay (t1), at the end of the 9-week home training phase (t2), and 3 months after the end of the accompanied training (t3: follow-up). Questionnaires and functional and clinical data are collected. After signing the informed consent, patients will be randomly allocated to the intervention group (including 2 subgroups arms; unimodal and multimodal intervention) or the control group (treatment as usual) using a 2:1 ratio. The subgroup allocation within the intervention group, either to a unimodal or a multimodal therapy will follow the Risk Stratification Index (RSI) [11]. An additional assignation to modules within the multimodal group will follow the Risk Prevention Index (RPI-S) [11] (see Figs. 1, 2, and 3.). The initial random 2:1 ratio allocation should ensure enough patients in each subgroup arm (unimodal or multimodal) to be able to analyze the differences between both and confirm the discrimination’s ability of the screening tool in this population (see Fig. 4). The framework of the trial is superiority.

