### Outcomes {12}

#### Risk stratification

##### Risk Stratification Index (RSI) and Risk Prevention Index (RPI-S)

The Risk Stratification Index (RSI) is a screening tool that allows an estimation of the risk of low back pain chronicity (1-year prognosis) through psychosocial risk factors. It includes baseline pain, unhappiness, social support and status, distress (chronic worries), work dissatisfaction, misfortune, pain persistence, sleep problems, and other health care issues such as medication history and insurance status [11].

The Risk Prevention Index (RPI-S) is a screening tool that identifies further individual therapy needs of low back patients, based on the risk within four psychosocial domains (distress, pain experience, social environment, and medical care environment). It also incorporates expectations to exercise treatments [11].

Both screening tools were derived through LASSO (least absolute shrinkage and selection operator) models, which covered yellow, black, and blue flag factors for chronic back pain and disability, as well as demographic and protective factors [32].

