### Participant timeline {13}

The main outcome of interest is pain measured as Characteristic Pain Intensity and Disability Score. The trial is divided into three phases: [1] 3 weeks stay in rehabilitation, [2] 9 weeks of supervised aftercare home training (training support by phone and digital media assistance), and [3] 12 weeks of independent aftercare home training. As shown in Fig. 4, measurements will take place at four time points in each group, at baseline (T0), directly before leaving the rehabilitation stay (T1), after 9 weeks of supervised aftercare home training (T2), and after 12 weeks of independent aftercare home training (T3).

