## Assignment of interventions: allocation

### Sequence generation {16a}

The method of generating the allocation sequence consists of computer-generated random numbers. A stratified randomization per center is conducted. Concretely, a block randomization with a fixed block size is planned for each center. After assigning a random number (generated by Excel) to a list of numbers (block size), the blocks are sorted by their random number, resulting in a random 2:1 assignment to the intervention or control group for each center at each time point.

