## Statistical methods

### Statistical methods for primary and secondary outcomes {20a}

Data is analyzed at the end after T3 data collection completion. Then, an examination of underlying assumptions for parametric or non-parametric hypothesis testing is applied. For the primary outcome pain (DISS, CPI), an analysis of variance (ANOVA) repeated measures for three time points (T0, T2, T3) between the groups (intervention vs control group) with covariates adjustment is planned. The covariates to include in the analysis are center, age, and sex. A complete case analysis is intended.

For secondary outcomes (psychometric items), missing value imputation follows only (in case of psychometric scores) the specific test manuals. Likewise, variance analytical testing is proposed. A sensitivity analysis is planned for concomitant therapy, such as medications.

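### The baseline RSI is neither stratified on nor adjusted for in the primary comparison, and its scoring in controls is not stated: a forgone gain in precision and robustness

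*Protocol article*

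**What the plan says.** All references are to the protocol article.

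- **Who is screened.** The abstract states that "participants in the intervention group will be screened according to their psychosocial risk profile". No section says that controls are scored, and none says that they are not.
- **Use of the score.** Under Trial design {8}: "The subgroup allocation within the intervention group, either to a unimodal or a multimodal therapy will follow the Risk Stratification Index (RSI". This happens after randomization.
- **What the score is.** The Outcomes section says the RSI "is a screening tool that allows an estimation of the risk of low back pain chronicity (1-year prognosis) through psychosocial risk factors". On its content: "It includes baseline pain, unhappiness, social support and status, distress (chronic worries), work dissatisfaction, misfortune, pain persistence, sleep problems", followed by medication history and insurance status.
- **Randomization.** Under Sequence generation {16a}: "A stratified randomization per center is conducted". No other stratification factor is named.
- **Baseline data.** Under Participant timeline {13}: "measurements will take place at four time points in each group, at baseline (T0".
- **Primary model.** Section {20a} plans "an analysis of variance (ANOVA) repeated measures for three time points (T0, T2, T3) between the groups (intervention vs control group) with covariates adjustment", and then: "The covariates to include in the analysis are center, age, and sex". The same section intends a complete case analysis.
- **Subgroup models.** Section {20b} adds baseline pain to age and sex, but not the RSI.

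**The concern.** The trial rests on the idea that psychosocial risk at admission predicts how back pain develops. The article has a score built for that prediction and uses it to steer treatment, but the primary intervention-versus-control comparison makes no use of it. Age and sex are the only patient-level covariates. If the RSI predicts pain intensity and disability beyond the planned covariates, the estimate is noisier than the baseline data would allow, in a trial planned around an effect as small as d = 0.2.

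Two features of this trial add some weight. The Discussion concedes that numbers are sent out several at a time, so that the therapist can sometimes foresee the next allocation. The primary analysis is complete-case, with 30% dropout assumed. In both situations the risk mix of the analyzed arms may depend on more than the random sequence, and adjusting for a prognostic baseline score gives partial protection. The article does not show that either problem has occurred.

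**Working it through.** **1. The plan's own figure.** Inputs from Sample size {14}: d = 0.2 (so f = d/2 = 0.1), m = 3 time points, correlation ρ = 0.57, alpha 5%, power 80%. For the between-group test in a repeated-measures ANOVA the noncentrality is λ = f²·N·m / (1 + (m − 1)ρ).

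- Equal allocation: N = 562 gives λ = 0.01 × 562 × 3 / 2.14 = 7.88 and power 80.0%. So 562 is the 1:1 total, or 281 per arm.
- Keeping 281 controls and doubling the intervention arm gives 562 + 281 = 843, and 843 / 0.7 = 1204.3, the stated 1204. The section prints 289 controls, but 562 + 289 = 851; 281 is the figure that fits and is used here.
- The group-by-time interaction with the same inputs needs only 140, so the between-group test lies behind 843.

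**2. Power before any adjustment.** For 2:1 allocation λ is multiplied by 4 × (2/3) × (1/3) = 0.889. At N = 843, λ = 11.82 × 0.889 = 10.5 and power is 89.9%. Solved directly for 2:1, the same inputs need 632.

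**3. Adding the RSI to the between-group test.** Let r be the correlation of the RSI with the subject mean after the planned covariates. The article gives no value, so 0.1 to 0.5 is assumed. Residual variance is multiplied by 1 − r², the standard error by √(1 − r²), and λ is divided by 1 − r².

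| r | 1 − r² | Fall in SE | N with the precision of 843 unadjusted | Power at 562:281 |
|---|---|---|---|---|
| 0.1 | 0.99 | 0.5% | 835 | 90.2% |
| 0.2 | 0.96 | 2.0% | 810 | 91.1% |
| 0.3 | 0.91 | 4.6% | 768 | 92.4% |
| 0.4 | 0.84 | 8.3% | 709 | 94.2% |
| 0.5 | 0.75 | 13.4% | 633 | 96.2% |

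**4. If the T0 outcome is already accounted for.** The RSI contains baseline pain, so part of its information is then already used. With a T0–T2 outcome correlation of 0.57, an RSI–T0 correlation r₀ and an RSI–T2 correlation r₂, the partial correlation is (r₂ − 0.57·r₀) / √[(1 − r₀²)(1 − 0.57²)]. Its square is the share of residual variance removed (r₀ and r₂ assumed):

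| r₀ | r₂ = 0.3 | r₂ = 0.4 | r₂ = 0.5 |
|---|---|---|---|
| 0.30 | 2.7% | 8.5% | 17.6% |
| 0.50 | 0.0% | 2.6% | 9.1% |
| 0.57 | 0.1% | 1.2% | 6.7% |

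The range is 0% to 18% of variance. The largest value is a fall in SE of 1 − √(1 − 0.176), about 9%.

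**5. Chance imbalance.** The arm difference in a standardized RSI has SD √(1/562 + 1/281) = 0.073, with 95% of differences within ±0.143. Multiplied by r = 0.1 to 0.5, the typical shift in the estimate is 0.007 to 0.037 SD of the analyzed response.

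**The case against.** The strongest reply is that a prespecified model with the stratification factor, age and sex is valid, and that adding a more efficient covariate is a choice. That stands: nothing here is an error of inference.

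A reader might infer three stronger claims that the article does not support.

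- *Controls are not scored.* The abstract sentence explains how intervention patients are routed. The Outcomes section describes the RSI without limiting it to an arm, T0 measurements are taken in both arms, and the allocation flow charts are not available in the text reviewed. The article is silent on controls.
- *Chance imbalance in risk biases the result.* Under randomization, imbalance in an omitted covariate is part of the random error that the standard error and the 5% level already cover. At this sample size it is also small (step 5).
- *The RSI is the strongest known predictor, so the loss must be large.* The article does not rank predictors. It describes a one-year chronicity score, whereas the main time point T2 falls after about 12 weeks. It also wants the trial to confirm that the tool discriminates in this population.

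Two technical replies also have force. T0 is one of the repeated levels, so in a group-by-time contrast a constant RSI effect cancels and only the part that changes over time matters. In the between-group test, however, T0 is averaged into the response and does not serve as an adjuster, so the reply does not remove the gain in the test that was used for sizing. Second, a covariate can cost patients in a complete case analysis: if 3% of completers had no usable RSI, the loss would cancel the gain for any r up to about 0.17 (1 − r² = 0.97). This is a reason for a missing-item rule.

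**Conclusion.** The point holds as a forgone gain in precision and robustness. The stated randomization and the stated primary covariates leave out the score that the article itself presents as prognostic, and its scoring is described for the intervention group only.

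The size cannot be taken from the article and rests wholly on assumed correlations. It is a 0.5% to 13% lower standard error in the between-group test, with power going from about 90% to 90–96%. Where the T0 outcome already carries the information, the RSI removes 0% to 18% of residual variance. It would be wrong to present this as rescuing a trial that has only 80% power: the arm sizes that reproduce 843 already give about 90% for d = 0.2 in that test.

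Foreseeable allocations and a complete case analysis with 30% assumed dropout are a modest further reason to adjust, but they do not show a biased result. This verdict concerns the randomized comparison only, not the comparison of the unimodal and multimodal subgroups with controls.

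**What to change.** 1. State in the abstract and under Trial design {8} that the RSI is scored from T0 items in both arms by the same rule, and that only intervention patients are routed by the result.
2. Add the T0 RSI score to the covariates in {20a}, giving center, age, sex and RSI, for both co-primary outcomes. If the repeated-measures form is kept, include RSI by time.
3. Fix a rule for missing RSI items, so that the complete case analysis does not drop patients only because the covariate is missing.
4. Record the change in a dated amendment before outcomes are compared by arm.

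The cost is small: a few sentences, scoring of controls, and one or a few degrees of freedom out of more than 800. Most ingredients appear to be covered by instruments described without restriction to an arm (CPG, BSSS, TICS, VE, ILE and the medication question). Insurance status is not visibly among them, so the sponsor should confirm which RSI items controls have answered. Any item not collected in controls would have to be handled by the missing-item rule.

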**Discussion:**

An improvement in terms of pain, work ability, patient compliance, and acceptance in our intervention program compared to the standard aftercare is expected. The study contributes to provide individualized care also to patients living far away from clinical centers.

**Trial registration:**

DRKS, DRKS00020373. Registered on 15 April 2020

**Supplementary Information:**

The online version contains supplementary material available at 10.1186/s13063-021-05823-3.

## Introduction

### Background and rationale {6a}

Chronic diseases are the main burden on the German healthcare system, and low back pain (LBP) is one of the most common ones [1]. Back pain is frequently associated with limited physical ability, sickness-related absence from work, and high socio-economic costs [2–4].

In Western Europe, low back pain was the highest contributor to disability (years lived with disability) and overall burden of disease (disability-adjusted life years) compared to 290 other conditions, according to the Global Burden of Disease 2010 Study [1]. In Germany 2017, LBP was also the leading cause of disability (years lived with disability) and the second most common cause of overall burden of disease (disability-adjusted life years) [2]. Considering 2019/2020 estimations, the 1-year prevalence of any type of back pain in Germany was 61%, while the lifetime prevalence of chronic back pain was 16% [5].

Moreover, the mean duration of incapacity for work in Germany is about 12.6 days. Back pain caused almost 6% of these days, being the second most important single medical diagnosis to contribute to incapacity [3]. Direct and indirect costs of back pain in Germany 2015 resulted in a cumulative estimation of approximately 4.5 billion (thousand million) euros (EUR) [4]. In the Berlin-Brandenburg region, a quarter of the days of incapacity for work are due to musculoskeletal disorders, lasting as long as 23 days [6]. The estimated loss of productivity per year in the region for about 20 days of incapacity for work rounds the 4.3 billion EUR [6].

Furthermore, psychosocial factors play a significant role in the development of chronic pain syndromes [7], including low back pain [8]. In line with the biopsychosocial model, LBP is better explained by the interaction between psychological, physical, and social factors than by the single anatomical or physiological model [9]. According to the national health care guidelines for the diagnosis and treatment of non-specific low back pain recommendations [10], an early screening of psychosocial risk factors is vital for an optimal therapy design (unimodal vs. multimodal). Until now, a lack of practical screening instruments for the early identification of individual needs regarding exercise interventions has been described. The recently published screening tool named Risk Stratification Index (RSI) [11] enables an estimation of the chronicity risk by means of psychosocial factors, supplemented by the Risk Prevention Index (RPI-S). The RPI-S additionally allows the identification of risk components in four psychosocial areas (pain experience, stress, medical care context, care context) [11]. Both screening tools aim to inform about the individual need for further psychosocial services and if specific supplementary training, physiotherapy, and/or psychosocial components are needed in order to increase intervention efficiency [12].

In rehabilitation ambulatory care, a multidisciplinary approach combining medical, physiotherapeutic, and psychological fields has already been introduced in Germany. However, its application has been challenging in diverse areas, and individualization of the therapy is still missing [10]. Its implementation has not reached most rural areas [10] and has to date been limited only to rehabilitation clinics and centers [13]. More often, no rehabilitation center is located in areas with low infrastructure; hence, the offer is missing in around 60% of the cases in Germany [10, 13, 14]. Until now, aftercare measures have been underused or were not easily accessible [14]. To our knowledge, no offer of an individualized home-based rehabilitation program is available. It is therefore of the greatest interest to assess these programs in the context of rehabilitative measures.

### Objectives {7}

This is a study on rehabilitation aftercare for back pain patients.

The aim of the study is to evaluate whether and how well an individually tailored rehabilitation aftercare program for back pain patients works. The following hypotheses are going to be examined:
An individualized and home-based aftercare program is more effective than regular outpatient rehabilitation aftercare in terms of pain reduction.An individualized and home-based aftercare program is more effective than regular outpatient rehabilitation aftercare in terms of work ability.An individualized and home-based rehabilitation aftercare leads to better patient compliance and more sustained intervention effects than regular outpatient rehabilitation aftercare.An individualized and home-based rehabilitation aftercare could be implemented and incorporated long term (feasibility) in the regular rehabilitation aftercare routines of the German Pension Insurance.

### Trial design {8}

Multicenter intervention trial: A randomized controlled prospective longitudinal intervention study (RCT) will be conducted at several hospitals in the regions of Berlin-Brandenburg and Central Germany. The study includes a total of four measurement points: at rehabilitation clinic admission (t0: baseline), at the end of the rehabilitation stay (t1), at the end of the 9-week home training phase (t2), and 3 months after the end of the accompanied training (t3: follow-up). Questionnaires and functional and clinical data are collected. After signing the informed consent, patients will be randomly allocated to the intervention group (including 2 subgroups arms; unimodal and multimodal intervention) or the control group (treatment as usual) using a 2:1 ratio. The subgroup allocation within the intervention group, either to a unimodal or a multimodal therapy will follow the Risk Stratification Index (RSI) [11]. An additional assignation to modules within the multimodal group will follow the Risk Prevention Index (RPI-S) [11] (see Figs. 1, 2, and 3.). The initial random 2:1 ratio allocation should ensure enough patients in each subgroup arm (unimodal or multimodal) to be able to analyze the differences between both and confirm the discrimination’s ability of the screening tool in this population (see Fig. 4). The framework of the trial is superiority.

**Fig. 1 Fig1:**
[figure not shown]
Flow chart of the study procedure

**Fig. 2 Fig2:**
[figure not shown]
Flow chart of the intervention allocation

**Fig. 3 Fig3:**
[figure not shown]
Flow chart of the Risk Stratification Index (RSI) allocation procedure into the unimodal or multimodal arm

**Fig. 4 Fig4:**
[figure not shown]
Schedule of enrollment, interventions, and assessments

Status: currently recruiting and in follow-up.

Dates of recruitment: 21.09.2020 to 31.12.2021. Dates of follow-up: 28.01.2021 to 17.06.2022

### Eligibility criteria {10}

Inpatients with back problems (ICD-10 diagnosis M50-54), 25 to 60 years old, admitted to one of the six rehabilitation clinics in Germany will be included.

Patients who had a surgery less than 6 months ago, have an acute infection or cold, or are pregnant will be excluded. Patients with an inflammatory rheumatic disease, severe neurological disease (e.g., dementia ICD-10 F00-F03, Alzheimer’s disease, epilepsy), severe psychiatric illness (e.g., schizophrenia ICD-10 F20, dysthymia F34.1), emotionally unstable personality disorders such as borderline disorders (ICD-10 F60.3x), intellectual limitations (such as ICD-10 F70 to F79), and diseases which contraindicate physical activity or participants who are unable to stand on one leg will be also excluded. Furthermore, limited knowledge of the German language is an exclusion criterion. (The trial targets employed patients who could return to work).

